## Discussion

Evidence on the role of the cerebellum in social cognition is rapidly increasing, showing that a dysfunction of core predictive mechanisms could impact on high-level social-cognitive abilities, such as Theory of Mind and the processing of social stimuli [15, 19]. These findings are in line with clinical reports on the importance of behavioural, affective and social skill alterations presented by patients with cerebellar diseases [12, 31, 60, 61]. Though, available rehabilitative interventions for these pathologies typically address motor and cognitive alterations [26, 28–30], but not social cognition deficits. Our study tries to fill this gap, proposing a protocol that aims to improve social prediction skills.

Rehabilitation treatments based on specific neural mechanisms of the brain offer the opportunity to design interventions with a clear rationale, but they also directly serve as a clinical validation of theoretical knowledge on brain functioning [62]. Other researchers have developed a brain-based VR treatment for adult patients [63], while VR-Spirit is a rehabilitative protocol targeted at children, adolescents and young adults specifically designed on the core predictive mechanism of the cerebellum. Notably, this kind of interventions appears particularly important in this developmental age group as it could benefit from natural brain plasticity [64, 65], fostering an effective impact on the quality of life and social participation of these patients.

The study design provides for an active control group that participates in a training in VR, playing games already adopted for motor rehabilitation. On one hand, this approach allows us to verify the specificity of the social prediction training in improving social cognition abilities. On the other, it enables us to investigate the effects of VR interventions on other cognitive abilities indirectly involved in the two trainings. Indeed, intrinsic features of VR systems, such as the natural sense of presence, the movement in attractive scenarios and the delivery of complex, multisensorial feedbacks, could enhance visual-spatial ability and sensorimotor integration [32]. However, since both the experimental and the control trainings engage motor systems, any differential outcome of the VR-Spirit vs. the control training is unlikely to reflect motor symptom improvements. Nevertheless, any change in sensorimotor functions as assessed by NEPSY-II subtests should be considered and controlled when analysing and discussing the outcomes of the study.

The VR-Spirit protocol provides a new kind of interventions for neurorehabilitation of patients with cerebellar malformations. While it fills a gap of rehabilitation on social cognition, it is worth mentioning that this approach could only partially address the rehabilitative needs of children, adolescents and young adults with congenital cerebellar diseases, which should necessarily encompass other interventions focussed on the motor [66] and cognitive deficits typically shown by these patients [61]. However, VR-Spirit is a first step to design future rehabilitative protocols targeted on the different clinical manifestations of CCAS.

The literature has widely documented cerebellar engagement in social cognition tasks in both low-level and high-level processing [15, 67]. Accordingly, we could reasonably assume that VR-Spirit activates the cerebellum along with other cortical areas involved by social inference [20]. Although, we did not directly verify this hypothesis. Future studies should consider adopting neurophysiological measures (e.g*.* electroencephalography) in order to investigate whether and how the cerebellum and other cortical areas are engaged by our paradigm.

Previous research has suggested that an intensive, goal-directed treatment could be at least as effective as one administered over a longer time and it could also be more acceptable by patients and their parents [26]. Although our protocol is in line with the state of the art in this field, the short duration and the required hospitalisation may limit the possibility of controlling the efficacy of this intervention on everyday life. Further, the use of expensive technology makes it difficult to replicate and extend the training to a wider sample. Future research may implement the VR-Spirit training using more accessible and wearable devices (e.g. X-Box Kinect and VR head-mounted displays), that allow it to be administered it in more ecological contexts.

The GRAIL technology is a medical device with 93/42EEC certification provided with safety equipment to prevent any risk associated with its use. However, VR treatments could be accompanied by unwanted side effects such as nausea and headache, which are referred to as simulator sickness or cyber sickness [68]. Although previous studies adopting GRAIL demonstrated its acceptability by clinical paediatric samples [40, 69], in case a participant should present cyber sickness symptoms the session will be interrupted until their sickness ends. Any episode of cyber sickness will be recorded by the GRAIL therapist and considered for evaluating the feasibility and acceptability of the intervention.

Finally, it is noteworthy that the participants are randomly allocated to the two groups, but the psychologist administering the neuropsychological evaluation, the GRAIL therapist and the parents of the patients are not blinded to the typology of interventions. As what concerns randomisation, the use of stratified randomisation has been issued for introducing biases when baseline features of all participants are not available before assignment [70]; nevertheless, it allows control of the effects of influencing covariates in a small sample size [71]. Moreover, while we reduced as much as possible the strata based on the importance of the clinical variables, the availability of patients for our sample may not consent to fulfilling all the blocks [47]. These methodological issues should be considered and discussed when evaluating and interpreting the results of the protocol. The results on efficacy and feasibility will be published in international peer-reviewed journals. Preliminary data on efficacy and feasibility will be submitted when at least half of the target sample has been recruited. Final efficacy results will be submitted within 6 months after the end of the trial.

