### Participants

Participants are children, adolescents and young adults aged 7–25 years with congenital cerebellar malformations and with a Full-scale Intelligent Quotient (FSIQ) greater than 45. Cerebellar malformations refer to anatomical abnormalities affecting the vermis and/or the hemispheres not due to acquired lesions and not associated with progressive pathologies. However, it is noteworthy that these patients could exhibit malformations in other cortical structures. As an example, patients with Joubert syndrome often present with malformations of the pontine and medullary areas [46]. Participants are recruited at the Child Neuropsychiatry and Neurorehabilitation Unit of the Scientific Institute, IRCCS E. Medea. With the aim of achieving the target sample size, associations of patients can be contacted. The following exclusion criteria have been adopted:
Severe sensorial, motor and/or behavioural problems that could interfere with the use of GRAIL technologyBeing simultaneously involved in a different cognitive rehabilitation treatment, to avoid excessive demands to children and possible interference on training adherence ratesHaving been involved in a different cognitive rehabilitation treatment in the last 6 months before training, to avoid confounding follow-up effects

Parents of all known potentially eligible patients are contacted telephonically by the attending physician and are informed about the aims and methods of the protocol. If they agree with the study, an administrative staff member contacts the parents to organise the recovery. Since participation in the trial has to be arranged according to other clinical needs (e.g. routine medical checks) of the patients and to parents’ availability, a variable time frame from 1 month to 1 year could occur before patients get access to the trial. Intervention assignment is carried out by a research assistant only when patients are admitted to the recovery. It is noteworthy that the administrative staff that attends to the recruitment and organises hospitalisation is blinded to group allocation. Before starting any study procedures, a research assistant provides a description of the material and procedures to parents and patients and asks them to sign an informed consent.

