### Outcome measures

Primary outcome measure:
Social prediction ability: performance during the pre- (T0) and post-training (T2) evaluation in the sweet stands’ scenario; standardised beta-coefficients of the regression between accuracy and probability in the testing phase of the validated PC-based Action Prediction task administered before/after the intervention (T0, T2) and at the follow-up visit (T3)

Secondary outcome measures:
Social cognition: Theory of Mind Parts A and B and Emotion Recognition of the NEPSY-II testing batteryImplicit learning: accuracy and reaction time in the familiarisation phase of an Action Prediction taskExecutive functions (inhibition and flexibility): Inhibition test of NEPSY-IIVisual attention: Visual Attention test of NEPSY-IIVisuospatial and visual-perceptual abilities: Geometric Puzzle and Picture Puzzle tests of NEPSY-IIMemory: Memory for Drawings test of NEPSY-IISensorimotor functions: Finger-tapping of NEPSY-IIBehavioural problems: CBCL 6–18, Parent versionOverall functioning and quality of life assessed using the TACQOL questionnaire, presented in two forms: the self-compiled one and the parent-compiled one

To assess training feasibility:
Number of dropouts: number of children who renounce to complete the 2-week trainingNumber of sessions completed per child: total number of sessions performed in front of the total number proposed of eight sessions

To assess training acceptability:
Acceptability questionnaire: an ad-hoc questionnaire completed by participants and another one by their parents after training conclusion (T2) to assess subjective evaluation of training accessibility and efficacy. It is to note that the same questionnaires are fulfilled by the patients of the active control group and their parents

A psychologist, who is not blinded to the intervention assignment, administers all the neuropsychological tests and questionnaires and records the performance during the GRAIL sessions.

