### Statistical methods

Demographic, clinical and neuropsychological variables of the two groups of patients are inspected through descriptive statistics. A *t* test and *χ*^2^ are used to assess the differences between the experimental and control training groups at baseline for continuous and categorical variables, respectively, thus allowing us to verify successful randomisation. For each outcome measure, we calculate the change between T0 and T2 (training effect delta) and between T0 and T3 (follow-up effect). Delta is calculated as the arithmetic difference between the second/third time points and the first time point. The delta values of the two groups for the primary outcome measure are compared using independent sample *t* tests (two-tailed). For the primary outcome measure, a Bonferroni correction procedure will be used to control for multiple comparisons. Multivariate analysis of variance will be used to explore differential effects of the trainings in the secondary outcome measures. As to what concerns missing data, a modified intention-to-treat analysis approach will be adopted, including in the analyses all the participants who had completed the pre- and post-treatment evaluation sessions, even if they had not completed all the training sessions. No imputation of missing data, however, will be used considering the limited sample size and observation points [58, 59]. The stratification factors (i.e. age and FSIQ), will not be considered in the statistical analyses, assuming that the stratification procedure has ensured a balanced distribution across the two groups.

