## Trial status

This protocol has been applied to ISRCTN registry on 12 January 2018, registered on 12 March 2018 and last edited on 20 December 2018. Recruitment started in February 2018 and will be continuing until August 2020 and is currently recruiting.

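### The protocol commits to submitting preliminary efficacy data from half the sample while recruitment continues and the assessor, therapist and parents are unblinded; the main risk is bias, and the type I error risk is conditional

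*Protocol article*

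**What the plan says.** The Discussion sets out two efficacy reports. The first is early: "Preliminary data on efficacy and feasibility will be submitted when at least half of the target sample has been recruited". The second follows completion: "Final efficacy results will be submitted within 6 months after the end of the trial". Under Trial status, enrolment is still open: "Recruitment started in February 2018 and will be continuing until August 2020 and is currently recruiting".

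On blinding, Outcome measures states: "A psychologist, who is not blinded to the intervention assignment, administers all the neuropsychological tests and questionnaires". The same person records performance in the GRAIL sessions. The Discussion adds that "the GRAIL therapist and the parents of the patients are not blinded to the typology of interventions". The only people described as blinded are in Participants: "the administrative staff that attends to the recruitment and organises hospitalisation is blinded to group allocation".

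Statistical methods defines the primary comparison as a two-tailed independent-samples t test of the two groups' change scores. Its one multiplicity rule is: "For the primary outcome measure, a Bonferroni correction procedure will be used to control for multiple comparisons". Estimation of sample size uses a single test at alpha 0.05.

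**The concern.** The sentence on preliminary data carries no condition. It does not say that the early report will be pooled over arms, that it will be descriptive only, or that by-arm results will be kept from people still treating and assessing patients. Since efficacy in this trial is an arm comparison, carrying out the sentence as written would most naturally put such a comparison into circulation with up to half of the patients still to be enrolled or assessed.

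Two things are at stake. The first is bias. Knowing a patient's arm is one thing; also knowing which arm is ahead is another, and it can colour how tests are given and how parents rate their child. Participants allows 1 month to 1 year between contact and entry, so families who are waiting could also learn the result before deciding to join. The second is the status of the early result: with two efficacy reports and no statement of which one is confirmatory, a significant finding at either could be presented as evidence of efficacy.

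**Working it through.** **Inputs.** From Estimation of sample size: 21 per group, d = 0.8, two-tailed alpha 0.05, target power 0.80. From the Discussion: earliest release at half the target, 21 of 42 patients, or 10 to 11 per group (information fraction t = 0.5). The number of Bonferroni comparisons is not stated; 2 and 3 are assumed below.

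**The plan's own figure.** A two-tailed t test with d = 0.8, alpha 0.05 and power 0.80 needs 26 per group by the noncentral t. At 21 per group the power is 0.716. A one-tailed test gives 21. That discrepancy is a separate matter; it is noted because 0.716 is the baseline used below.

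**Two looks, each at two-sided 0.05.** Under the null, the interim and final statistics are approximately bivariate normal with correlation √t. Overall type I error = 1 − P(|Z₁| < 1.96 and |Z₂| < 1.96).

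| Information at first report | Correlation | Type I error if either report counts |
|---|---|---|
| 0.50 | 0.707 | 0.083 |
| 0.60 | 0.775 | 0.080 |
| 0.75 | 0.866 | 0.073 |

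A simulation of 400,000 trials with t tests (11 v 10 patients, then 21 v 21) also gave 0.083 for either look. The final test alone gave 0.050.

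**Does the Bonferroni rule cover this?** With 2 comparisons, each is tested at 0.05/2 = 0.025; two looks at that level give 0.043 per comparison. With 3, each is tested at 0.0167; two looks give 0.029. Adding these gives an upper bound on the family-wise error of 2 × 0.043 = 0.086 or 3 × 0.029 = 0.087, where Bonferroni at a single look guarantees 0.05. The rule deals with several comparisons, not with repeated looks.

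**What a half-sample result can show.** The smallest significant observed effect is d = t(0.975, 2n − 2) × √(2/n):

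- n = 10: 2.101 × 0.447 = 0.94
- n = 11: 2.086 × 0.426 = 0.89

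Power for a true d of 0.8 is 0.40 at n = 10 and 0.43 at n = 11. So a significant early result in favour of VR-Spirit must exceed the planned effect; if the true d is 0.8, significant early results average about 1.29 (simulation). A non-significant early result is more likely than not even when the planned effect is real.

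**Where bias can enter.** No arithmetic applies here.

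- NEPSY-II is given by an unblinded psychologist, and CBCL and the parent form of TACQOL are completed by unblinded parents. All are secondary outcomes, and all are open to influence.
- The VR evaluation score is logged by the D-flow software, and the Action Prediction coefficient comes from a computer task. Both are primary measures and are less exposed, although encouragement during testing could still act on them.
- Willingness to join and to stay is exposed whatever the outcome.

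**The case against.** The strongest reply is that the sentence promises less than it may seem to. It mentions neither arms nor a test, it separates preliminary data from final results, and the protocol states no stopping or decision rule at half sample. If only the final test is confirmatory, its error stays at 0.05 however many descriptive reports precede it. This stands, and it makes the 0.083 conditional.

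Other parts also stand. Half is a floor, so the first report may come later, with a smaller inflation. Submission is not publication, so how many patients would be untested when results became known cannot be said. The tester, therapist and parents already know the allocation, and the Discussion says that this must be weighed in interpretation. The primary measures are computer-recorded.

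The last part of the reply is that interim boundaries are commonly left to a full protocol or analysis plan, which is not shown. Their absence from an article is indeed no fault. But the release is fixed here without condition, and a boundary set elsewhere would not undo the effect of publishing an arm comparison mid-trial.

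A reader might go further and infer an unplanned interim analysis, or no control of alpha at all. The document supports neither: the release and its earliest time are announced, and a Bonferroni rule exists for the primary outcome.

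**Conclusion.** The point holds as a fault in the dissemination sentence. As written, it permits, and most naturally means, release of an arm comparison from as few as 21 of 42 patients during recruitment, with the assessor, therapist and parents unblinded. That the release is by arm is an inference from how the protocol defines efficacy, not its wording.

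The main consequence is bias, chiefly in NEPSY-II, CBCL and TACQOL and in recruitment and retention. Its size cannot be computed from the document. The type I error consequence is secondary: about 0.083 at half information and 0.073 to 0.080 at 75% to 60%, for a single measure tested at 0.05, and only if significance at either report is treated as a finding. It would be wrong to conclude that the trial's false-positive rate necessarily exceeds 5%. Separately, with power of 0.40 to 0.43, the early comparison would be a poor guide to the effect.

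**What to change.** Reword the sentence in the Discussion so that the mid-trial report covers feasibility and acceptability only (dropouts, sessions completed, cyber sickness, acceptability questionnaires), pooled over arms. State that no by-arm efficacy result will be released until the last patient's T3 visit, and that the final analysis is the sole confirmatory test. This leaves alpha at 0.05 with no adjustment and no loss of power. The cost is a sentence or two of text and a delayed early efficacy paper; feasibility results can still appear early.

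If an interim efficacy test is to be kept, state an O'Brien-Fleming-type boundary. For one interim look at half information, the nominal two-sided levels are about 0.0052 and then 0.0480, and final-test power at 21 per group for d = 0.8 falls only from 0.716 to 0.709. If the Bonferroni rule also applies, these levels must be derived from the alpha given to each comparison. Such a boundary protects the type I error only. It does not remove the bias from publishing the comparison, so the interim result would also have to be kept from the people treating, testing and enrolling patients.

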## Trial status

This protocol has been applied to ISRCTN registry on 12 January 2018, registered on 12 March 2018 and last edited on 20 December 2018. Recruitment started in February 2018 and will be continuing until August 2020 and is currently recruiting.

## Data Availability

Data are collected in a protected database and are anonymised, as a research member assigns to each participant an identity number that substitutes the name. Participants’ parents give written informed consent to anonymised data use. The anonymised data are available on request by sending an email to [name] ([contact]). All data will be available for 5 years after the relevant publication.

## Abbreviations

CBCL: Child Behaviour Check List
CCAS: Cerebellar cognitive affective syndrome
FSIQ: Full-scale Intelligent Quotient
NEPSY-II: Developmental NEuroPSYchological Assessment, 2nd edition
TACQOL: Tno-Azl (Netherlands Organisation for Applied Scientific Research Academic Medical Centre) Children’s Quality Of Life questionnaire
VR: Virtual reality
WISC-IV: Wechsler Intelligence Scale for children, 4th edition
